## Abstract

**Background:**

Evidence from multiple pilots and post-introduction scale-up initiatives have demonstrated that self-administered subcutaneous depot-medroxyprogesterone acetate (DMPA-SC) has potential to improve contraceptive continuation rates and expand contraceptive access to populations with limited utilization of facility-based health services. Only a few of these studies have been conducted in South Asian countries, and none where most contraceptive use is of non-hormonal methods that require limited to no contact with the health system, leaving policymakers in countries like Pakistan with limited context-specific evidence to guide decisions on whether, how, and for whom to introduce DMPA-SC.

**Methods:**

A prospective cohort study will be conducted in 41 health facilities and surrounding communities in Punjab, Pakistan. The primary objective of the study is to compare the 12-month contraceptive continuation rate for women who receive DMPA-SC with that for women who receive intramuscular depot-medroxyprogesterone acetate (DMPA-IM). The secondary objectives are to compare characteristics and experiences of participants who opt for DMPA-SC with those of women who opt for DMPA-IM, which must be administered by a health worker. Additionally, a sub-study is planned to assess how well women opting for self-injection of DMPA-SC adhere to standards for commodity storage, injection timing, injection technique and waste disposal.

**Discussion:**

This research offers an opportunity to contribute to global efforts to reduce inequities in access to contraceptive method choices, while generating actionable evidence to inform health sector decision-making in Pakistan. Although study sites are limited to health facilities where a woman’s first self-injection of DMPA-SC is supervised by a nurse, midwife, medical officer, Lady Health Visitor, Family Welfare Worker or Family Welfare Councilor, the research protocol and findings will provide a foundation for future studies testing alternative service provision and self-injection support models.

**Trial registration:**

Registered on clinicaltrials.gov as an observational study (NCT05774626).

**Supplementary Information:**

The online version contains supplementary material available at 10.1186/s12905-025-03969-9.

## Background

Depot medroxyprogesterone acetate (DMPA) is a highly effective family planning method that requires administration every three months for continued contraceptive protection [1]. Recent estimates suggest that injectables are currently used by more than 72 million women worldwide and, while injectables are the most common modern contraceptive method in sub-Saharan Africa, they are less common in other geographic regions [2]. However, science is continuously evolving; continued investments in contraceptive technology have led to emergence of new contraceptive methods, formulations and designs with the aim of improving availability and accessibility of contraceptive choices that meet the needs of women and men around the world [3]. Among these advancements is the introduction of a subcutaneous formulation of DMPA (DMPA-SC), which is therapeutically equivalent and has a similar safety profile as the syringe-administered intramuscular formulation (DMPA-IM) but is administered through the Uniject system with a smaller needle and slightly lower hormonal dose [4].

In recent years, evidence has demonstrated that self-injection of DMPA-SC is safe, feasible, acceptable, can lengthen method continuation, and expands contraceptive accessibility to groups with lower health service utilization rates [5]. For example, a 2019 meta-analysis found higher rates of continuation with self-administration of injectable contraception compared to provider administration, and found no difference in reported pregnancies across arms [6]. World Health Organization (WHO) guidelines for sexual and reproductive health self-care interventions promote scale-up of self-administered DMPA-SC as part of strategies to reduce unmet need for contraception and achieve universal access to sexual and reproductive health [7], and there are numerous governments, foundations and civil society organizations around the world involved in DMPA-SC introduction efforts [8].

As research priorities shift from effectiveness trials and pilot studies to implementation research embedded in introduction and scale-up processes, context is a critical consideration [4, 5, 9]. The majority of studies demonstrating potential for DMPA-SC to improve contraceptive access, continuation and autonomy in low-and-middle income countries were conducted in sub-Saharan Africa where, regionally, injectable contraception already comprises the largest share of the method mix [2]. (Table 1) Few have been conducted in contexts like Pakistan where the contraceptive prevalence rate (CPR) has stagnated, and where the most commonly used contraceptive methods are male condoms (27% of all users), female sterilization (27% of all users), and withdrawal (23% of all users)—all methods that require no or one-time contact with health providers and are non-hormonal, and two of which are coital-dependent and male-controlled. Within this context, DMPA-SC is particularly novel as a hormonal, female-controlled, and multi-month acting method. These differentiating features, alongside a collective interest to understand and meet contraceptive needs of women and couples of Pakistan, make DMPA-SC worthy of exploration [10]. The most recent Pakistan Demographic and Health Survey (2017–2018) further illustrates gaps in meeting individuals’ contraceptive needs; one-third of married women who are not using contraception intend to do so in the future, and 56% of women who discontinue use within 12 months of starting a contraceptive method do so because of reasons other than wanting to become pregnant (e.g. method-related reasons, health concerns, cost, inconvenience, etc.) [10]. The potential for DMPA-SC to improve contraceptive continuation, autonomy and experiences in Pakistan has not been studied extensively. Past studies have assessed Lady Health Worker competence in DMPA-SC initiation [11], client satisfaction [12], and the role of non-governmental organizations in promoting DMPA-SC as a means of self-care [13], but none have examined continuation rates or potential of DMPA-SC to reach new users with interests in delaying or avoiding pregnancy.

**Table 1 Tab1:** Studies measuring DMPA-SC continuation rates in low-and-middle income countries, 2015–2023*

Author (Year), Title	Country	Study arms	Selected outcomes
Cohort studies			
Hernandez et al. T. (2023). Task-shifting and family planning continuation: contraceptive trajectories of women who received their method at a community-based event in Kinshasa, DRC [14]	DR Congo	• Women receiving a modern contraceptive during community-based FP campaign (including DMPA-SC administered by a nursing student)	• 6-month and 9-month continuation rate • Determinants and reasons for discontinuation
Nai et al. (2022). What Distinguishes Women Who Choose to Self-Inject? A Prospective Cohort Study of Subcutaneous Depot Medroxyprogesterone Acetate Users in Ghana [15]	Ghana	• Self-injected DMPA-SC • DMPA-SC administered by family planning providers	• 6-month and 9-month continuation rate • Determinants and reasons for discontinuation
Sherpa et al. (2021). A prospective cohort study to assess the acceptability of Sayana Press among 18–49-year-old women in Nepal [16]	Nepal	• DMPA-SC administered by family planning providers • DMPA-IM administered by family planning providers	• Client satisfaction • 6-month and 9-month continuation rate
Cover et al. (2019). Continuation of self-injected versus provider-administered contraception in Senegal: a nonrandomized, prospective cohort study [17]	Senegal	• Self-injected DMPA-SC • DMPA-IM administered by family planning providers	• 12-month contraceptive continuation rate • Determinants and reasons for discontinuation
MacLachlan et al. (2018). Continuation of subcutaneous or intramuscular injectable contraception when administered by facility-based and community health workers: findings from a prospective cohort study in Burkina Faso and Uganda [18]	Burkina Faso, Uganda	• DMPA-SC administered by CHW in Uganda and by family planning providers at health facilities in Burkina Faso • DMPA-IM administered by CHW in Uganda and by family planning providers at health facilities in Burkina Faso	• 12-month continuation rate
Cover et al. (2018). Continuation of injectable contraception when self-injected vs. administered by a facility-based health worker: a nonrandomized, prospective cohort study in Uganda [19]	Uganda	• Self-injected DMPA-SC • DMPA-IM administered by nurses at public health facilities	• 12-month continuation rate • Determinants and reasons for discontinuation
Cover et al. (2017). Evaluating the feasibility and acceptability of self-injection of subcutaneous depot medroxyprogesterone acetate (DMPA) in Senegal: a prospective cohort study [20]	Senegal	• Self-injected DMPA-SC	• Self-injection competency at 3-months post-training • Acceptability of DMPA-SC self-injection at 3 months post-training (for those discontinuing at that time) and 6-months (for those continuing) • Home storage and disposal practices
Cover et al. (2017). A prospective cohort study of the feasibility and acceptability of depot medroxyprogesterone acetate administered subcutaneously through self-injection [21]	Uganda	• Self-injected DMPA-SC	• Self-injection competency at 3-months post-training • Timeliness of reinjection
Randomized Control Trials			
Burke et al. (2018). Effect of self-administration versus provider-administered injection of subcutaneous depot medroxyprogesterone acetate on continuation rates in Malawi: a randomised controlled trial [22]	Malawi	• Self-injected DMPA-SC • DMPA-SC administered by family planning providers	• 12-month continuation rate • Determinants and reasons for discontinuation • Adverse events

^*^Articles identified through a PubMed search using strategies outlined in Kennedy et al.’s systematic review and meta-analysis on self-administration of injectable contraception published in 2019 [6]

As the government and other stakeholders in Pakistan seek to expand the reach and range of contraceptive options available to meet the population’s needs, context-specific evidence can help guide strategy development and resource allocation. Further research is needed to understand how and where DMPA-SC self-injection may help address unmet need for contraception in Pakistan, including potential differences in DMPA-SC and DMPA-IM user profiles and factors that will support and hinder continuation. Such insights may be critical to provincial decision-makers considering benefits and costs of expanding service offerings to include DMPA-SC for self-injection, particularly where uptake of injectable contraceptive uptake is low and per-unit procurement costs of DMPA-SC are higher than that of DMPA-IM [23].

## Methods/design

### Study design

This will be a non-randomized prospective cohort study. We calculated the sample size necessary to detect a 10% difference in 12-month continuation rates between DMPA-SC and DMPA-IM users with 80% power at 0.05 level of statistical significance. Assuming equal preference for each injectable method, a 12-month continuation rate of 50% for DMPA-IM users, and a retention rate of 75% follow-up following the 4th injection (the equivalent of 12-months of contraceptive coverage), a total of 500 participants are needed in each intervention group. Thus, we anticipate enrolling a total of 1,000 women (500 DMPA-SC clients and 500 DMPA-IM clients).

### Study setting and site selection

Pakistan’s administrative divisions include four provinces (Balochistan, Kyber Pakhtunkwa, Punjab, Sindh), two autonomous territories (Azad Jammu Kashmir, Gilgit-Baltistan) and a federal capital territory (Islamabad), which are further divided into districts, tehsils (sub-districts), and union councils (villages). Health sector governance was decentralized in 2010–11, with a constitutional amendment placing responsibility for health policy, financing and implementation with provincial authorities [24].

This study will be conducted in Punjab province where the modern contraceptive prevalence rate (mCPR) among married women is 27% [10]. One in six married women in Punjab has an unmet need for family planning, and demand satisfied by modern methods is 50% [10]. Mirroring national trends, the modern contraceptive method mix among married women is dominated by male condom use (28% of contraceptive users) and female sterilization (27%). Injectables contribute 6% of the modern method mix [10].

A total of 41 health facilities were selected as study sites across two districts of Punjab, Kasur and Khanewal. These districts were selected in consultation with the Government of Punjab to represent two of the three administrative regions of Punjab (Central and Southern) and based on the following criteria: mix of urban and rural populations, existing utilization of injectable contraceptives and functional government structures. The government-recommended districts of Kasur and Khanewal were endorsed by the project’s Steering Committee. Health facilities were purposively selected as study sites by study team members, in consultation with local authorities, to reflect variations in location (urban/rural), ownership (Department of Health, Population Welfare Department, private sector), and facility type (district headquarter hospitals, tehsil headquarter hospitals, rural health centers, basic health units, family health clinics, family welfare centers, and private clinics).

### Support for family planning service provision

Study team members will visit each selected health facility to confirm staffing, availability of a family planning service delivery area with space for self-injection training, an appropriate storage space with at least three-month supply of family planning commodities (to mitigate risk of stock-outs during the anticipated enrollment period), and a secure location for storage of study documents. If a selected health facility is unable to demonstrate readiness for study implementation, an alternative of the same type may be identified in collaboration with local authorities. All family planning service providers at selected facilities will receive a three-day training, followed by supportive supervision visits, to ensure that they have the necessary knowledge and skills to counsel clients on a full range of contraceptive methods, screen clients according to the WHO’s Medical Eligibility Criteria (MEC), administer DMPA-IM, DMPA-SC, and effectively coach women to self-inject, calculate their reinjection date, and adopt proper waste management techniques. Community health workers serving populations in facility catchment areas will also receive a one-day training on DMPA-SC, MEC and injection techniques to enable them to support self-injection clients, and, together with male social mobilizers, support community engagement activities to generate awareness about the new family planning method and its availability in study districts. Study team members will conduct routine supportive supervision and monitoring visits to confirm continued readiness for family planning service provision and fidelity to counseling and service provision protocols. In the event that a facilities experiences a stock-out during the enrollment period, recruitment of clients will be paused at that site until commodities are supplied and readiness is again confirmed. Once enrollment targets are met, the study team will continue to monitor family planning service provision at these facilities but will not intervene in the management of commodities supplied by the Department of Health or Population Welfare Department.

### Study population

All married women of reproductive age who receive family planning counseling at a participating health facility who choose and are medically eligible to receive injectable contraception will be given an option of either DMPA-IM (current health worker administered standard of care) or DMPA-SC (new administration method, with option for self-injection after completing training). As Fig. 1 shows, those opting for DMPA-SC will receive training on self-injection procedures and an opportunity to practice injection procedures on a model (e.g. condom filled with salt) to demonstrate confidence and competency. The health worker will assess client competency using a standardized checklist; if it is demonstrated, the client will be given the opportunity to inject herself under the supervision of a health worker during the visit. If competency is not demonstrated, or the client does not feel confident enough to self-inject, the health worker will administer the DMPA-SC injection. Both clients that demonstrate competence, and clients who do not demonstrate competence or are lacking confidence to self-inject but remain interested to do so will then be shown how to use a calendar to determine when their next injection is due. Each client will receive a take-home packet that includes an Urdu-language calendar, a pictorial job aid booklet illustrating and the steps for self-injection, safe and appropriate storage, and disposal (Additional file 1), plus three units of DMPA-SC. The job aid booklet also includes a link and QR code that brings users to an animated video demonstrating the same so that they can review self-injection steps at their own time and pace at home. DMPA-SC users will also be advised that they can seek support from community health workers to learn and practice self-injection techniques, and/or seek assistance with administration of their next dose if they still do not wish to self-inject.

**Fig. 1 Fig1:**
[figure not shown]
Family planning service provision and cohort study recruitment flow chart

#### Inclusion and exclusion criteria

All married women aged 18–49 who receive family planning counseling at a participating health facility and who either receive DMPA-IM or receive DMPA-SC and are given additional doses to take home for future use will be eligible for enrollment in the prospective cohort study. Additionally, to be eligible to participate in the study, women must be residents within the study districts and be willing to be contacted by study team members, either in-person or via telephone.

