#### Data analysis

Characteristics (e.g. demographics, contraceptive history, reasons for methods choice, reproductive empowerment measured using a validated scale developed by MEASURE Evaluation [25], general self-confidence) and experiences of women enrolled in DMPA-SC and DMPA-IM study arms will be compared using *t* tests for continuous variables and chi^2^ tests for categorical variables. Differences in contraceptive continuation rates of DMPA-IM and DMPA-SC users will be compared at each follow-up point (6,9 and 12-month continuation rates) using Kaplan–Meier survival analysis methods and factors associated with risk of discontinuation analyzed using a Fine-Gray subdistribution hazard model.

Additional descriptive analyses of DMPA-SC user characteristics and experiences may include comparisons of the proportion of clients opting for DMPA-SC who successfully self-inject their first dose under the supervision of a provider; if assistance is sought for subsequent injections; what type of assistance is sought, and from who; and confidence in self-injection capacity.

DMPA-SC client adherence to storage, injection timing, and waste disposal standards will also be measured using descriptive statistics, with sub-analyses comparing differences in adherence based on household demographics, location and access to health services.

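### Eligibility does not separate new from established DMPA users in either arm, and the stated comparison of 12-month continuation takes no account of prior DMPA use

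*Protocol article*

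**What the plan says.** All places are in the protocol article.

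- **Inclusion and exclusion criteria.** Eligible women are those "who either receive DMPA-IM or receive DMPA-SC and are given additional doses to take home for future use will be eligible". The further conditions are residence in the study districts and willingness to be contacted. Prior use of DMPA is not mentioned.
- **Study population.** Women who choose an injectable and are medically eligible are offered "DMPA-IM (current health worker administered standard of care) or DMPA-SC (new administration method, with option for self-injection after completing training". The offer does not depend on what they used before.
- **Support for family planning service provision.** Community activities are meant to "generate awareness about the new family planning method and its availability in study districts".
- **Study setting and site selection.** The criteria for choosing districts include "existing utilization of injectable contraceptives and functional government structures".
- **Study design.** The sample size assumes "a 12-month continuation rate of 50% for DMPA-IM users", a 10-point difference, 80% power, a 0.05 level and 75% retention, and arrives at 500 per group. The fourth injection is treated as completing 12 months of coverage.
- **Cohort intake and follow-up.** Time runs from the injection at enrolment, and later injections are numbered second and third from it.
- **Data analysis.** "Characteristics (e.g. demographics, contraceptive history, reasons for methods choice" and other items are compared between arms with t tests and chi-squared tests. Continuation is compared at 6, 9 and 12 months "using Kaplan–Meier survival analysis methods and factors associated with risk of discontinuation analyzed using a Fine-Gray subdistribution hazard model".

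**The concern.** Women who have already had several DMPA injections have shown that they tolerate the drug and can keep to its schedule. Those who would have stopped early are no longer among them. If the risk of stopping falls with time on the method, continuation counted from a mid-course injection will be higher than continuation counted from a first injection.

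The numbering of injections fits a woman who starts at enrolment. For a woman already on DMPA-IM, the study's fourth injection may be her sixth or tenth. The 12-month continuation rate then averages two different quantities, in proportions that may differ between arms.

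Because women choose their arm, nothing in the design balances prior experience. Comparing contraceptive history between arms would reveal an imbalance but would not remove it from the Kaplan–Meier contrast. At stake is the primary objective, the 12-month comparison of DMPA-SC with DMPA-IM.

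**Working it through.** **1. Can established users enter each arm?**

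- *DMPA-IM arm.* The eligibility rule has no new-user condition, DMPA-IM is existing care, and the districts already use injectables. Recruitment runs January to June 2024 and DMPA is given every three months, so a client who keeps to schedule would have about two reinjection visits in that window. The rule can therefore reach current users.
- *DMPA-SC arm.* The product is new to the districts, but the drug need not be new to the woman. A current DMPA-IM client is offered DMPA-SC on the same terms as anyone else. The Background describes the two formulations as therapeutically equivalent with similar safety, so a woman who switches also brings established tolerance.

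Both arms can mix starters and experienced users. The document gives no share for either arm and no continuation rate for experienced users.

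**2. The plan's own figure.** For 50% against 60%, two-sided 0.05 (sidedness is not stated, so this is assumed), 80% power and unpooled variance:

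n = (1.960 + 0.842)² × (0.5×0.5 + 0.6×0.4) / 0.10² = 7.849 × 0.49 / 0.01 = 384.6, so 385 per group.

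Allowing for 75% retention: 385 / 0.75 = 513.3, so 514, which is 2.8% above the stated 500. Conversely, 500 × 0.75 = 375 evaluable per group, with power 78.7%. The sample size is broadly reproduced and is not the point at issue.

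**3. Effect of unequal shares.** Let f and g be the shares of DMPA-experienced women in the DMPA-IM and DMPA-SC arms, and k the number of points by which they continue more often than starters, taken as the same in both arms. With a true difference of 10 points:

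observed difference = 10 + k × (g − f).

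The values of f, g and k below are assumptions for illustration. Power is at 375 per group, starting from 50% against 60% in starters.

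| f (IM) | g (SC) | k | IM | SC | Difference | Power |
|---|---|---|---|---|---|---|
| 10% | 0 | 10 | 51% | 60% | 9 points | 70% |
| 20% | 0 | 20 | 54% | 60% | 6 points | 38% |
| 30% | 0 | 20 | 56% | 60% | 4 points | 20% |
| 30% | 0 | 30 | 59% | 60% | 1 point | 5% |
| 30% | 15% | 20 | 56% | 63% | 7 points | 50% |
| 30% | 30% | 20 | 56% | 66% | 10 points | 80% |
| 0 | 30% | 20 | 50% | 66% | 16 points | over 99% |

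The sign of the bias is the sign of g − f, which the document does not determine.

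**4. Cost of restricting to new or restarting users.** If 30% of the DMPA-IM arm and 10% of the DMPA-SC arm were experienced (assumed), restriction leaves 375 × 0.7 ≈ 262 and 375 × 0.9 ≈ 337 women. Power for 50% against 60% is then about 69%. At 60% and 20%, it leaves 150 and 300, with power about 52%.

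**The case against.** **The stronger reading.** A reader might infer that survivors sit only in the comparator, because every DMPA-SC user starts a new product, so that DMPA-IM continuation is inflated and a benefit of DMPA-SC is hidden. The document does not support this. DMPA-SC is a new product but not a new drug, and current DMPA-IM users may choose it. Bias against DMPA-SC is plausible if established users mostly stay with what they know. It is absent at equal shares, and it reverses if switchers concentrate in the DMPA-SC arm. Any single range for the bias depends on the shares put in.

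**Enrolment of established users is permitted, not stated.** Entry depends on counselling and on choosing a method. Whether routine reinjection visits pass through that route may be shown in the recruitment flow chart, which was not available for this review. This stands as a limit on certainty. It does not supply the missing condition, since recruitment covers each client who receives an injectable.

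**Covariates and strata belong in an analysis plan.** An article may leave them there, and the Fine-Gray model could include contraceptive history. This has some force. However, eligibility and the start of follow-up are fixed in this text. The method that it names for the arm comparison is Kaplan–Meier, and it gives the Fine-Gray model the separate task of examining factors associated with discontinuation.

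**All-comer enrolment is defensible.** The study is meant to inform introduction decisions, and who chooses each method is itself a secondary question. This stands. It argues for keeping everyone in and stratifying, and against narrowing the cohort.

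**Conclusion.** The concern holds in a direction-neutral form. The eligibility rule mixes new, restarting and established DMPA users in both arms, and the stated comparison of 12-month continuation between self-selected groups does not separate them. A difference between arms in prior DMPA experience would bias the primary contrast by k × (g − f) points.

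No figure for that bias can be taken from the document. Under the assumed values above, a true 10-point difference would appear as anything from 1 to 16 points, and as exactly 10 when the shares are equal. The conclusion rests on two assumptions: that experienced users continue more often than starters, and that some of them enrol. Both are reasonable, but neither is stated. The point should be addressed before the primary analysis, because a crude difference could not be read with confidence in either direction.

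**What to change.** 1. Classify every woman in both arms at enrolment as a new/restarting or a continuing DMPA user. One workable definition of new/restarting is no injectable in the previous 120 days, which matches the protocol's own discontinuation limit. The contraceptive history listed under Data analysis should supply this. The intake tool was not available for this review, so the sponsor should confirm that it records current or recent injectable use.
2. State that the primary 12-month comparison is stratified by, or adjusted for, this variable. For example, combine the within-stratum Kaplan–Meier differences at 12 months with prespecified weights.
3. Report the size of each stratum by arm, and the 12-month continuation in each stratum.
4. Show the comparison restricted to new/restarting users as a sensitivity analysis only, because of the loss of power shown above.

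The cost is a short addition to the analysis text and slightly more analysis work. If the intake tool holds the item, no new data are needed. Stratification loses no participants, but the stratum-specific estimates will be less precise than the pooled one.
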